### 3.2. Participants

The participants, as already indicated, belong to the ASPACE association (adults) and the Director Mercedes Sanromá Special Education School (children). The study will involve 40 subjects: 20 adults and 20 children. The following criteria are proposed for this group of participants.

#### 3.2.1. Inclusion Criteria

People with a recognized disability, caused by a disease or permanent health situation.Aged between 2 and 65 years.Have a degree of functional ability in the mobility domain that is categorized as moderate–low. For adult participants, this will be determined through items related to their motor functionalities according to the International Classification of Functioning, Disability and Health (ICF) [29]. For children, it will be determined using the Gross Motor Function Classification System (GMFCS), ref. [30] and Manual Ability Classification System (MACS) [31]. In [32] a study of this population was conducted and the two scales were homogenized to measure adults and children in the same way.People with motivation to use technologies and/or who can use wearable devices during the intervention time.People who come weekly to the collaborating centers.

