## Abstract

Background: The protocol described in this paper is part of a research project coordinated between three Spanish universities, where a technology aimed at improving the quality of life of people with cerebral palsy will be developed. Part of the proposed technology will consist of an interface and a series of applications to increase motivation for daily physical activity. The basis of these developments is the measurement of the emotional state of the subjects. Methods: The experimental protocol is designed with two research objectives, on the one hand to identify the emotional state through physiological signals, and on the other to determine whether music can be a motivating factor to promote physical activity. It is specifically designed for subjects with cerebral palsy, taking into account the special characteristics of this population. These are people with whom it is difficult to use questionnaires to have a basis to contrast with the measured physiological signals, so measurements must be taken in carefully chosen daily-life situations. Discussion: We hope our findings show which physiological parameters are the most robust to measure the emotional state and how to design rehabilitation and physical activity promotion routines that are motivating, in addition to being able to avoid risk factors during the performance of these routines. Trial registration: NCT05621057.

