## 1. Introduction

Physical activity is recommended at all ages and for both healthy people and people with functional diversity. The World Health Organization recommends it and even places special emphasis on children and adolescents. In the particular case of people with CP, it is of particular importance. It has demonstrated benefits for motor functions, including enhancing gait speed [1], spasticity [2], balance [3] and muscle strength [4]. It is therefore desirable to find procedures that increase motivation and help to improve the times and routines that this population dedicates to exercise. Detecting the emotional state and fatigue that a subject may have is important, although in this type of population the detection of these states is difficult given individuals’ communication difficulties.

The objective of this experimental protocol is to determine the relationship between physiological measurements and emotional state in children and adults with cerebral palsy (CP). Our research goal is to collect objective and robust information (based on biosignals) about the user’s condition to improve the effectiveness of rehabilitation therapies and the promotion of physical activity, and to determine whether music can improve these outcomes. The knowledge of the user’s emotional state is important to conduct the appropriate activities for their rehabilitation.

The experimentation will be conducted with a group of users belonging to the Association of People with Cerebral Palsy of Seville (ASPACE) and the Director Mercedes Sanroma Special Education School of Seville.

The methodology will be applied to groups of users of different ages with different capacities. For this reason, we have designed a flexible methodology that proposes different tasks according to the context. Certain tasks require physical effort, a factor that must be considered given the potential disruption that it may cause in the data collected [5].

Having an emotional characterization of the user based on their physiological measurements will enable us to obtain a real-time evaluation of the user’s emotions while tasks are being performed. Consequently, activity can be improved by adjusting the required parameters for effective computation, leading to better results.

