#### 3.2.3. Recruitment of Participants

All people who meet the inclusion criteria will be invited to participate in the study. The recruitment of participants will be carried out by the TAIS (Technology for Assistance Integration and Health) research group of the University of Seville, through contact with the collaborating centers. In all cases, a cover letter will be delivered to the managers or directors of the centers with all the information about the project. The participants and/or their representatives will sign the informed consent form.

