## 5. Conclusions

People with CP have particular difficulties in recognizing both their mood and fatigue. This means that in rehabilitation routines or in the performance of physical activity, it is sometimes difficult to properly program the exercise so that they find it motivating and get the most out of the time devoted to such activity.

There are questionnaires that allow the measurement of both the emotional state [35] and the fatigue state [36], but a user with CP does not always have the necessary cognitive and communication skills to rely on these questionnaires.

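### The objective and conclusions concern people with cerebral palsy, but the eligibility criteria do not require that diagnosis, and for the children nothing else in the text secures it

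*Protocol article*

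**What the plan says.** The target population is named in three places. The Abstract says of the protocol: "It is specifically designed for subjects with cerebral palsy, taking into account the special characteristics of this population". The Introduction gives the objective as to "determine the relationship between physiological measurements and emotional state in children and adults with cerebral palsy (CP". Section 5 (Conclusions) opens with "People with CP have particular difficulties in recognizing both their mood and fatigue".

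Section 3.2.1 lists five inclusion criteria. The only one about the person's condition is "People with a recognized disability, caused by a disease or permanent health situation". The others are age 2 to 65, moderate–low function in mobility, motivation for technology and/or ability to use wearables, and attendance: "People who come weekly to the collaborating centers". Section 3.2.2 excludes people for incompatibility with the technology, very limited cognitive capacity, lack of human support, or hearing impairment. Neither list mentions CP.

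Section 3.2.3 then states: "All people who meet the inclusion criteria will be invited to participate in the study".

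On where participants come from, section 3.2 says that they "belong to the ASPACE association (adults) and the Director Mercedes Sanromá Special Education School (children". The Introduction shows that the adults' organisation is an association of people with CP. It describes the children's centre only as a special education school.

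**The concern.** The eligibility rule should define the population about which the study will speak. Here the rule is wider than the objective. A child at the school with another permanent disabling condition, suitable mobility and weekly attendance meets every listed criterion and would be invited.

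What is at stake is whom the results describe. In part 1, section 4.2 keeps the physiological variables that differ significantly between sessions 1 and 2 in a majority of participants, counted over everyone enrolled. Those variables are then used to judge the effect of music in part 2, where group-level tests are also run on all participants together. If the group is mixed, both the chosen variables and the group results belong to a mixed group, yet the article would present them as findings on CP.

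**Working it through.** **1. The texts side by side**

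| Element | Where | CP required? |
|---|---|---|
| Design intent | Abstract | Yes |
| Objective | Introduction | Yes |
| Conclusions | Section 5 | Yes |
| Inclusion criteria | Section 3.2.1 | No |
| Exclusion criteria | Section 3.2.2 | No |
| Invitation rule | Section 3.2.3 | No; all who meet the inclusion criteria |
| Source of adults | Introduction, section 3.2 | In effect largely yes (CP association), though membership is not a stated diagnosis |
| Source of children | Introduction, section 3.2 | Not stated (special education school) |

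The gap therefore lies mainly with the children: 20 of 40, half the sample. Section 4.1 works with 18 and 18 instead of 20 and 20, which is a separate discrepancy; the share is one half either way.

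**2. How many participants could be affected**

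Let f be the fraction of enrolled children without CP. The article does not give f, so this is a range and not an estimate. Taking all adults to have CP, participants with CP = 40 − 20f:
- f = 0: 40
- f = 0.25: 40 − 5 = 35
- f = 0.5: 40 − 10 = 30
- f = 1: 40 − 20 = 20

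**3. What the majority rule permits**

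Assume that a majority means at least 21 of 40. These are deliberately extreme cases, to show what the rule allows and not what is likely.
- f = 0.5 (30 with CP, 10 without): a variable significant in all 10 children without CP and in 11 participants with CP reaches 10 + 11 = 21 and is kept, although it worked in only 11/30 = 37% of those with CP.
- f = 0.5: a variable significant in 20/30 = 67% of those with CP and in no child without CP reaches 20 and is dropped.
- f = 0.25 (35 with CP, 5 without): 5 + 16 = 21 keeps a variable that worked in 16/35 = 46% of those with CP.

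**4. Does requiring CP disturb the sample-size argument?**

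Inputs from section 4.1: p = q = 0.5, 95% confidence (z = 1.96), margin e = 0.15, frame N of about 200 (100 per centre).

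n0 = z²pq/e² = 1.96² × 0.25 / 0.15² = 42.68

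n = n0 / (1 + (n0 − 1)/N) = 42.68 / (1 + 41.68/200) = 35.3, rounded up to 36. The article's figure reproduces.

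Now let only a share of the school's 100 children have CP (an assumption; the share is not given) and keep all 100 adults:

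| Share of school's children with CP | N | n |
|---|---|---|
| 100% | 200 | 36 |
| 75% | 175 | 35 |
| 50% | 150 | 34 |
| 25% | 125 | 33 |
| 0% | 100 | 31 |

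Restricting eligibility to CP barely changes the figure.

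**The case against.** The best defence is that section 3.2.1 should not be read alone. Section 3.2 introduces the criteria as applying to a group already described, and the Introduction sets the objective in CP. On that reading the list only filters a CP population fixed beforehand, and the fault is one of drafting. Part of this stands: the authors' intention is plainly CP. But what section 3.2 identifies is membership of the two centres, not a diagnosis, and the invitation rule in section 3.2.3 depends on the inclusion criteria alone. Nor do the functional classifications used for children settle it: the article uses them to grade mobility, manual ability and communication, and does not present a grade as proof of diagnosis.

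Other objections limit the point, and they are right. A reader might infer any of the following, and the article supports none of them:
- **That the sample will be mixed, or that 20 children will lack CP.** The article is silent on the school's diagnoses. Twenty is only the size of the child group, and f could be zero.
- **That diagnosis is confounded with the adult/child split.** Section 4.2 plans no comparison of adults with children, so no planned contrast would carry such confounding.
- **That the comparisons themselves are biased.** Session 1 against 2, and silence against music, are made within the participant. Everyone contributes to both sides, so diagnosis is balanced.
- **That the whole article speaks only of CP.** Later in the Introduction the problem is framed for people with severe disabilities, and the parent project concerns disabled people in general.
- **That a different response by diagnosis has been shown.** The study of children with CP described in section 2 compared them with typically developing children, not with children who have other disabilities.

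**Conclusion.** The mismatch is real and lies within the text shown. The criteria are set out in full, and as stated they do not define the population named in the Abstract, the objective and the Conclusions. It is not a detail left to a fuller document.

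Its reach is limited. It concerns chiefly the child half of the sample, by an amount that the article does not allow anyone to estimate. It affects the population to which the majority-based variable selection and the group-level tests apply, not the internal validity of the within-participant contrasts. The selection examples rest on assumed values of f and on reading a majority as at least 21 of 40. If every child enrolled has CP, the results are unaffected and only the wording needs repair. The change should be made, because as written nothing ensures that this is so.

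**What to change.** Add a documented diagnosis of cerebral palsy to the inclusion criteria in section 3.2.1.

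If the broader population is what the investigators intend, then instead: record each participant's diagnosis at entry, base conclusions about CP on the participants who have it (including the majority count that selects variables), and describe pooled results as applying to people with motor disability. The objective should then be worded to match.

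The first option costs one line and possibly a smaller pool of eligible children at the school. The second costs one recorded item per participant and, if some children do not have CP, a smaller group behind the CP conclusions. Neither upsets the sample-size reasoning in section 4.1.

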#### 3.2.2. Exclusion Criteria

Presenting a health situation that is incompatible with the use of technology (e.g., use of respirator, pacemaker, sensitive skin).Have a very limited cognitive capacity that prevents the individual from following the instructions for the proper use of assistive technology. For adults, this will be measured through relevant items in the ICF scale, and for children through using the Communication Function Classification System (CFCS) [33].Not having adequate human support.People with hearing impairments.

#### 3.2.3. Recruitment of Participants

All people who meet the inclusion criteria will be invited to participate in the study. The recruitment of participants will be carried out by the TAIS (Technology for Assistance Integration and Health) research group of the University of Seville, through contact with the collaborating centers. In all cases, a cover letter will be delivered to the managers or directors of the centers with all the information about the project. The participants and/or their representatives will sign the informed consent form.

### 3.3. Instruments of Measurement

#### 3.3.1. Tests and Questionnaires

In this subsection, we present tests and questionnaires to determine the basic state of each participant or those to be used before and after the intervention with the participants. It is important to know the quality of life and emotional situation of the subjects to be measured, with the aim of subsequently contrasting the physiological measurements taken. There are two populations: children and adults. In addition, the cognitive status of the subjects may vary. All of these are factors to be taken into account when applying the measurement instruments. Sometimes, depending on the abilities of individual participants that may prevent them from completing the questionnaires independently, their family members or the professionals of the centers will be responsible for completing the questionnaires.

ICF for the adult population [29].MACS [31] for children.GMFCS [30] for children.CFCS [33] for children.KIDSCREEN Questionnaire (accessed on: https://www.kidscreen.org/english/questionnaires/, accessed on 10 May 2024): Will be used in its 10-item version for the evaluation of the child population; it is an instrument that measures the quality of life related to health.Musical Preferences Questionnaire: This measure will ask about songs that motivate the subjects and generate a positive and active emotion. Music serves as a catalyst to enhance the enjoyment of the activity. Hence, understanding the musical preferences of the individual user is crucial. The objective is not to employ a uniform, neutral piece of music for all participants and examine its isolated impact.EVEA scale and free text to be filled in by caregivers or relatives. The EVEA scale, according to [26], is consistent and has the ability to detect changes in mood. This scale will be used at the beginning of the data recording once the sensors have been placed and at the end of recording time.

#### 3.3.2. Devices for Recording Physiological Data

During the sessions, we will use 4 wearable devices developed in the context of this project to collect data. Figure 1 shows a diagram of the sensors that will be used.

These are 4 devices that distribute sensors throughout the body, comprising 4 inertial units on the wrist, ankle, chest and head: a wrist temperature sensor; a sensor of the electrical activity of the skin (EDA) in the phalanges (using dry electrodes placed on the thenar and hypothenar eminences of the dominant hand); an electrocardiography sensor on the chest; and 16 channels of electroencephalography (EEG). In addition, the ambient temperature can be recorded.

One of the wearables we will use is the OpenBCI device (accessed on https://openbci.com/, accessed on 10 May 2024). It is a 16-channel bioamplifier for EEG measurement open-source and low-cost hardware that measures at a maximum rate of 125 Hz when 16 channels are used and includes an inertial unit that measures at 25 Hz. In Figure 2, the electrode position is indicated. The figure shows the positions of the electrodes included in the 10/20 system, which are FP1, FP2, F1, F2, F5, F6, Cz, C3, C4, T7, T8, Pz, P3, P4, O1 and O2. Additional reference and ground electrodes will be placed on the right ear and FPz positions, respectively. The system has been validated in various studies, and the electrode positions it utilizes allow for the measurement of all brain regions, providing sufficient information about the subject’s state.

We will analyze the data using the following independent variables according to the approved clinical trial (accessed on https://clinicaltrials.gov/study/NCT05621057, accessed on 10 May 2024):Average kinetic energy measurements (in joules) using inertial sensors to estimate energy expenditure in physical activity.Instantaneous heart rate (HR), in seconds. Ag/AgCl electrodes will be used for ECG and processing to extract RR segments from two consecutive beats. The position of the R wave is determined using an appropriate algorithm and then the time difference between two consecutive R waves is calculated. RR segments will be used to generate the heart rate variability (HRV).The ratio between the low-frequency and high-frequency (LF/HF) components of HRV. This variable shows the balance between the sympathetic and the parasympathetic nervous systems.Standard deviation of NN intervals (*SDNN*), Equation (1), root mean square of successive differences between normal heartbeats (*RMSSD*), Equation (2), and percentage of successive *RR* intervals that differ by more than 50 ms (*pNN50*), Equation (3), as temporal variables of HRV. The term “NN interval” that appears in these measurements is the result of removing outliers from the calculated series of *RR* intervals, which can lead to alterations in the measurements. u(n) is the Heaviside, or unit step function.
$$\bar{RR}=\frac{1}{N}\sum_{i=1}^{N}RR_{i}$$
(1)$$SDNN=\sqrt{\frac{1}{N}\sum_{i=1}^{N}{\left(RR_{i}-\bar{RR}\right)}^{2}}$$
(2)$$RMSSD=\sqrt{\frac{1}{N-1}\sum_{i=2}^{N}{\left(RR_{i}-RR_{i-1}\right)}^{2}}$$
(3)$$pNN50=\frac{100}{N-1}\sum_{i=2}^{N}u(|RR_{i}-RR_{i-1}\left|-50ms\right)$$Skin conductance level (SCL) and skin conductance response (SCR) to detect slow and fast variations in EDA, respectively.Fractal dimension (FD) of EEG to compute its complexity using Higuchi’s algorithm.The spectrum entropy (SE) of EEG is a tool to determine the EEG complexity. The initial step involves acquiring the power spectral density (PSD). The PSD is then normalized by the number of bins, effectively converting it into a probability density function. Finally, the traditional Shannon entropy for information systems is computed.EEG coherence. The interplay among neural systems, functioning within each frequency band, is approximated through EEG coherence. The amplitude of EEG is affected by neural synchronization, while the coherence of signals obtained by a pair of electrodes indicates the uniformity and steadiness of the signal’s amplitude and phase. A time delay in the signal should be observable between two interconnected brain regions, which is interpreted as a phase shift in the frequency domain.

Regarding the possibility of muscle activity influencing EEG signal measurements, it is important to note that the muscles engaged in the activity are typically distant from the openBCI, and thus their influence is negligible. EEG is more likely to be affected by facial muscles, head movements, etc. For such cases, Independent Component Analysis (ICA) will be utilized, as it is an efficient algorithm for source separation and artifact removal in EEG signals. The data will be recorded in a synchronized manner using a software application (Figure 3) designed for this purpose [34]. The software utilizes the LabStreaming Layer library. This library supplements each captured data point with a timestamp generated by a high-resolution local clock, simplifying data synchronization. Additionally, the library employs the Network Time Protocol (NTP) to estimate communication delays, thereby adjusting the time offset between clocks.

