## 3. Materials and Methods

### 3.1. Design of the Study

The first part of the study will be descriptive and observational where the choice of those parameters (dependent variables) that adequately characterize the emotional state of the subjects will be sought. The second part of the study will be analytical, where the influence of music on changes in the selected dependent variables will be determined. In this second part, a single case study will be made, type AB, for each subject, where in condition A the rehabilitation exercise is carried out in silence, while in condition B it is accompanied by motivating music.

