### 4.2. Data Analysis

In general, numerical variables will be expressed as mean (M) and standard deviation (SD), including range, minimum and maximum.

For the first part of the study, we will compare the dependent variables obtained between sessions 1 and 2 for each subject using the permutation test of the difference in means between different data windows. Those dependent physiological variables that mark significant differences for most of the subjects will be chosen. Changes in EVEA test responses between sessions 1 and 2 will serve as reinforcement for detecting the level of emotional change.

We will also correlate the results of the EVEA test with the base state questionnaires to determine the existence of some type of dependency between the base level of EVEA and its variation with respect to the base state. This dependence will be explored with the Spearman or Pearson correlation test.

For the second part, first, we will analyze the variation in EVEA for sessions 3 and 4 to determine if there is a significant dependence on the independent variable (music) between stages A and B for all the participants. We will use the Kruskal–Wallis test, which does not require any type of assumption regarding the normality and homoscedasticity of the samples. These variations will also be correlated with the quality of life scale (ICF, GMFCS, MACS, CFCS, or KIDSCREEN), as was carried out with the data from the first part.

For the physiological variables and the average kinetic energy, we will determine if their variations are significant between A and B by means of a Kruskal–Wallis test applied to the group of subjects, but also at the individual level by means of a permutation test.

The significance of the tests will be set at three levels, indicated with * (*p* < 0.05), ** (*p* < 0.01) and *** (*p* < 0.001).

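### Kinetic energy in unscaled joules, compared by an unpaired rank test that pools ages 2 to 65, lets body-size differences hide a music effect in children and adults alike

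*Protocol article*

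**What the plan says.** Section 3.3.2 of the protocol article defines the movement outcome as "Average kinetic energy measurements (in joules) using inertial sensors to estimate energy expenditure in physical activity". It gives the unit as joules and states no division by mass and no log or percentage scale.

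Section 3.2.1 admits people "Aged between 2 and 65 years", and section 3.2 plans the mix: "The study will involve 40 subjects: 20 adults and 20 children". Under section 3.1, "a single case study will be made, type AB, for each subject", so every participant is measured in both conditions, in silence and with music.

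Section 4.2 fixes the comparison: "For the physiological variables and the average kinetic energy, we will determine if their variations are significant between A and B", and this is to be done "by means of a Kruskal–Wallis test applied to the group of subjects, but also at the individual level by means of a permutation test". No split or stratification by age group is stated for the group test. For description, "numerical variables will be expressed as mean (M) and standard deviation (SD), including range, minimum and maximum". On error levels, "The significance of the tests will be set at three levels": 0.05, 0.01 and 0.001.

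Section 3.3.1 recognises children and adults as two populations, but only as a matter for applying the measurement instruments.

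**The concern.** Kinetic energy is the only outcome listed in section 3.3.2 that measures movement directly. One of the two stated objectives is whether music can promote physical activity, so this outcome carries that question.

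Two choices work against it. First, the same movement gives far more joules in a large body than in a small one, so much of the spread in the pooled data records body size. Second, the group test does not use the fact that each person serves as his or her own control. Kruskal–Wallis ranks all session 3 and session 4 values together as if they came from different people, so the size spread is not removed. A real effect of music on activity could then be reported as absent at group level.

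**Working it through.** **The plan's own figure.** The only sample-size figure is 36, from Cochran's formula in section 4.1. n0 = 1.96² × 0.25 / 0.15² = 42.68. With the finite-population correction, 42.68 / (1 + 41.68/200) = 35.3, rounded up to 36. It reproduces. It concerns the precision of a proportion and says nothing about power for kinetic energy.

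**Size ratio.** Kinetic energy is ½mv². For the same angular movement, v is proportional to limb length L, so joules scale with mL². The documents give no body sizes. Assumed examples:
- 10-year-old (32 kg, 1.38 m) against adult (75 kg, 1.70 m): (75/32) × (1.70/1.38)² = 2.34 × 1.52 = 3.56.
- Toddler (12 kg, 0.87 m) against the same adult: (75/12) × (1.70/0.87)² = 6.25 × 3.82 = 23.9. This is an extreme.

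**Why the planned test loses the signal.** Assume between-subject log SD 0.5 and log-ratio SD 0.4, which is a noise variance of 0.4²/2 = 0.08 per session. With equal groups, an adult-to-child ratio R adds (ln R)²/4 to the variance within each session. The effect of +40% is ln 1.4 = 0.336.

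| R | Variance per session | SD | Effect/SD | × √20 |
|---|---|---|---|---|
| 1 | 0.25 + 0 + 0.08 = 0.33 | 0.574 | 0.586 | 2.62 |
| 3.5 | 0.25 + 0.392 + 0.08 = 0.722 | 0.850 | 0.396 | 1.77 |
| 10 | 0.25 + 1.325 + 0.08 = 1.655 | 1.287 | 0.261 | 1.17 |

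The last column approximates the expected test statistic for an unpaired comparison of 40 with 40 values, to be set against 1.96. The paired log ratio gives 0.336/0.4 × √40 = 5.3 at every R.

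**Simulation under the same assumptions** (20 children and 20 adults, two-sided 0.05, +40% in everyone):

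| Group test | R = 1 | R = 3.5 | R = 10 |
|---|---|---|---|
| Kruskal–Wallis on joules (planned) | about 86% | about 24% | about 1% |
| Kruskal–Wallis on size-free values | about 86% | about 86% | about 86% |
| Paired test of the log ratio | nearly 100% | nearly 100% | nearly 100% |

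**Effect in one group only (+40%).** The planned test detects an effect confined to children in at most 0.3% of trials at ratios 3.5 to 24, and an effect confined to adults in no more than 0.2%. The loss is symmetric. The paired log ratio detects such an effect in about 65%.

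**How much is due to pairing.** At R = 1, with no size difference, Kruskal–Wallis detects a one-group +40% effect in 9 to 10% of trials and +20% in everyone in 15%. The paired log ratio detects them in about 65% and 76 to 79%. Scaling for size alone restores only the Kruskal–Wallis levels.

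**Other assumptions.** With within-subject SD 0.25 per session and +25% in everyone, the planned test has power 0.35, 0.02, 0.00 and 0.00 at R = 1, 3, 5 and 10. On size-free values it is 0.33 to 0.35, and with the paired log ratio about 0.97.

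**Descriptive mean.** With equal group sizes, adults supply R/(1 + R) of the mean joules: 75%, 83% and 91% at R = 3, 5 and 10.

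**The case against.** The strongest reply is that the plan already holds a sound within-person analysis. Section 3.1 frames the second part as a single-case study, and section 4.2 adds a permutation test for each individual. There a person's mass is constant and cancels, so an effect in a child can show in that child's own result. This stands, and it limits the point to the group-level comparison. It does not rescue that comparison, which the article states as a separate result.

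A second reply is that ranks bound the influence of large values. That is also right. A reader might infer that large adults dominate the group test, so that its answer is the adults' answer. The planned test does not support this: it hides an effect in adults as fully as one in children. Adult dominance holds only for the pooled mean and SD.

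A third reply is that the comparison may be of changes within each session, since section 4.2 speaks of variations. Those changes would still be in joules and still be compared unpaired, so the size problem remains.

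Finally, a reader might go further and say that kinetic energy is no measure of energy expenditure, that mass is never obtained, or that assisted movement would contaminate it. The documents do not support these as faults. The article claims only an estimate, the calculation may be given in the full protocol, and nothing states that any exercise is assisted.

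**Conclusion.** The point holds for the group test of kinetic energy. Unscaled joules, pooling of children with adults and an unpaired test together leave body size in the error term and can mask a music effect in both age groups. Body size and lack of pairing both contribute; for small or one-group effects the unpaired test is the larger fault, since it loses most of the power even when everyone is the same size.

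For +40% in everyone, detection falls from about 86% at equal size to 24% at a ratio of 3.5 and 1% at a ratio of 10, against nearly 100% with a paired log ratio. These figures rest on assumed log-normal data, SDs and size ratios, none of which the documents give. The direction is the same under both sets of SDs examined. The individual permutation tests are not affected.

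**What to change.** In section 4.2, replace the group Kruskal–Wallis test for average kinetic energy as follows:

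- For each subject, compute the log ratio of session 4 to session 3 kinetic energy at the same sensor sites, so that mass and limb length cancel. Gravity-removed acceleration magnitude can be used in place of kinetic energy.
- Test these log ratios against zero with a Wilcoxon signed-rank test or a sign-flip permutation test.
- Report the result for all subjects and also separately for children and adults.
- Keep mean and SD in joules as description, by age group and not pooled.
- Leave the individual permutation tests as they are.

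The cancellation requires the same exercise in both sessions for a given subject, which the AB design implies; one sentence should say so.

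The cost is wording and analysis code only, using data that will be recorded anyway. The group result becomes a relative change and is no longer in joules. A log ratio can be unstable in a subject who hardly moves in one session, which is a reason for choosing a rank or sign-flip test.
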